To evaluate the efficacy of Familias con Orgullo in preventing drug use and depressive symptoms, this study will use a randomized trial design with two arms (Familias con Orgullo and community practice; see study design and intervention conditions below). We hypothesize that Familias con Orgullo will be efficacious, compared to community practice, in decreasing past 90-day drug use frequency and quantity and depressive symptoms among HSMY, over 30-months and that the intervention effects on youth outcomes will be partially mediated by changes in parent support for the youth, parent acceptance, family functioning, youth stress, and sexual minority stress. In addition to our main hypothesis, this study also aims to explore whether gender and baseline levels of parent support for the youth, parent acceptance, family functioning, youth stress, and sexual minority stress moderate intervention effects on the youth outcomes. We hypothesize that gender and baseline levels of parent support for the youth, parent acceptance, family functioning, youth stress, and sexual minority stress will moderate intervention effects on youth outcomes such that youth at higher risk (e.g., families reporting higher stress, lower support, and poorer family functioning) will benefit most from Familias con Orgullo.

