#### Main effects

All analyses will be conducted in M*plus* which utilized Full Information Maximum Likelihood to handle missing data [36, 37]. To examine the efficacy of Familias con Orgullo, compared to community practice, in decreasing past 90-day drug use (frequency and quantity) and depressive symptoms among HSMY, over 30-months, we will use latent growth modeling (LGM) [38]. Growth models can be expressed in terms that are identical to multilevel models, where the first level fits each response in time to an individual-level growth model and the second level represents how the slope of outcomes (drug use and depressive symptoms) varies by condition. The second level represents the condition effect on the slope of outcomes (drug use and depressive symptoms). As recommended by Raudenbush and Bryk, we will use 2-level analysis to determine whether the mean trajectories of outcomes for Familias con Orgullo and control differ significantly over time [39]. To account for the non-independence of outcomes, we will conduct multivariate growth modeling similar to that used in evaluating a previous trial [40]. If correlations have above moderate effects (.30 < *r*) [41], we will empirically examine the distinct contributions of the intervention on each separate outcome, using false discovery rate to account for multiple comparisons. Data analysis for this hypothesis and all others will be conducted using M*plus* (v 8.8) [42].

M*plus* Monte Carlo simulation with 10000 replications [43] was used to calculate the power for the main effects outcomes using a latent growth curve model framework with one covariate (i.e., condition assignment) and missing data. With 4 time points and assuming equal sample sizes across both conditions (i.e., 153 cases in each condition) and 20% attrition rate, which is consistent with the attrition in our past studies [12], we have 80% power (assuming a Type I error = .05) to detect a regression coefficient equal to 0.12 (d = 0.36) in the regression of the slope growth factor (for both drug use and depression) on intervention condition. This is considered a small effect size [41, 43].

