To test whether gender and baseline levels of parent support for the youth, parent acceptance, family functioning, youth stress, and sexual minority stress moderate intervention effects on the outcomes, an interaction term between intervention condition and each of the potential moderators will be created and entered into a growth curve model by regressing the trajectory slope on condition, gender, and the potential baseline moderators, and their interaction. For probing the interaction effect, the Johnson-Neyman (JN) technique [47] will be used to assess where moderation occurred. The JN technique identifies regions of significance of intervention effects on the outcome trajectory. Based on the results of the JN technique, we will estimate two separate trajectory models to examine the intervention effects on each of the outcome trajectories. Also using Monte Carlo simulation analyses with 10000 replications, power analyses were conducted for this hypothesis using a moderation model framework. With a baseline sample size of 306 (assuming 20% attrition rate at each assessment time point), we have 80% power to uncover a significant moderation effect (p < .05) when the regression coefficient of the interaction is approximately |0.14| (i.e., *R*^*2*^ effect size were |0.02| for interaction effect), which is considered a small effect [41].

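### Refitting separate trajectory models on either side of a Johnson-Neyman boundary uses the same data to choose and to test the subgroups, so the exploratory moderation results will exaggerate subgroup contrasts

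*Protocol article*

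**What the plan says.** The moderation paragraph stands under *Main effects* in the protocol article's *Data analysis plan*. It sets out a sequence.

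1. Six moderators are named, gender and five baseline constructs: "To test whether gender and baseline levels of parent support for the youth, parent acceptance, family functioning, youth stress, and sexual minority stress moderate". Condition-by-moderator terms enter the regression of the growth slope.
2. JN then follows: "For probing the interaction effect, the Johnson-Neyman (JN) technique [47] will be used to assess where moderation occurred".
3. The article says what JN delivers: "The JN technique identifies regions of significance of intervention effects on the outcome trajectory".
4. The last step acts on that output: "Based on the results of the JN technique, we will estimate two separate trajectory models to examine the intervention effects".

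The *Introduction* gives the aim its status, "this study also aims to explore whether gender and baseline levels of parent support for the youth, parent acceptance, family functioning", and attaches a directional hypothesis that these factors "will moderate intervention effects on youth outcomes such that youth at higher risk" gain most.

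False discovery rate control is named earlier under *Main effects*, for separate outcomes. The moderation paragraph does not mention it.

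**The concern.** JN marks the moderator values at which the estimated effect differs significantly from zero. It does not mark where the effect differs between families. The standard error of the conditional effect grows with distance from the moderator mean, so a boundary can appear when every family has the same true benefit.

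Fitting a separate model on each side then reuses the data that placed the boundary. The inside group was chosen because its effect was significant, so a second significant result there is no new evidence and its estimate is too high. The outside group tends to be small or to carry the unfavourable noise, so its estimate is too low or its test has little power.

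At stake is the reading of the directional moderation hypothesis. A pair of refits showing benefit on one side only would look like confirmation that some families benefit and others do not, and the size of that contrast would come partly from the selection.

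**Working it through.** **Inputs from the article (*Main effects*).** N = 306, 153 per arm; 20% attrition; d = 0.36; Type I error 0.05; 80% power.

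**Step 1: reproduce the stated power.** Completers per arm: 153 × 0.8 = 122.4. Power ≈ Φ(d√(n/2) − 1.96) = Φ(0.36 × √61.2 − 1.96) = Φ(2.816 − 1.96) = 0.804. This matches the stated 80%, so d = 0.36 with about 245 completers is a fair setting for the check.

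**Step 2: why a boundary appears without moderation.** Take a standardised moderator m, equal arms and unit residual SD. The conditional effect is b₁ + b₃m, with standard error about (2/√n)√(1 + m²). Suppose the data come out exactly uniform (b₁ = 0.36, b₃ = 0) with n = 245:

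- At the mean: 2/√245 = 0.128, so z = 0.36/0.128 = 2.82.
- At m: z = 2.82/√(1 + m²), which falls to 1.96 when m² = (2.82/1.96)² − 1 = 1.07, so m ≈ ±1.03.
- For a normal moderator about 70% of youths lie inside and 30% outside, although the estimated effect is 0.36 everywhere.
- The outside group has about 0.30 × 245 = 74 youths, 37 per arm. Its power for d = 0.36 is about Φ(0.36 × √18.5 − 1.96) = Φ(−0.41) = 0.34. A non-significant result there mostly reflects its size.

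**Step 3: simulation of the planned steps with zero moderation.** Slope score = d·T + 0.2·M + N(0,1), M standard normal, 10,000 trials per row. Fit T, M and T×M, form the pointwise 5% JN region, split if 10-90% of youths fall inside, and refit the intervention effect in each part. The false pattern is p < .05 inside with p ≥ .05 outside.

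*JN run whether or not the interaction is significant:*

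| n | d | split made | false pattern, all trials | mean inside / outside, when split |
|---|---|---|---|---|
| 245 | 0.36 | 76% | 57% | 0.43 / 0.26 |
| 306 | 0.36 | 76% | 59% | 0.39 / 0.24 |
| 245 | 0.20 | 44% | 26% | 0.38 / 0.21 |
| 306 | 0.20 | 51% | 31% | 0.34 / 0.20 |
| 245 | 0 | 13% | 5.5% | −0.01 / −0.01 |
| 306 | 0 | 13% | 5.8% | −0.01 / 0.00 |

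A different split rule (at least 20 youths on each side) with a moderator coefficient of 0.3 gives 65-66% at N = 306 and 59% at about 244 completers, for d = 0.36. The range for d = 0.36 is therefore about 57-66%, depending on n and the split rule.

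*JN run only after an interaction with p < .05:*

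| n | d | split made | of those, false pattern | mean inside / outside |
|---|---|---|---|---|
| 245 | 0.36 | 4.7% | 93% | 0.54 / 0.07 |
| 306 | 0.36 | 4.9% | 96% | 0.51 / 0.07 |
| 245 | 0.20 | 4.7% | 69% | 0.43 / 0.02 |
| 306 | 0.20 | 5.1% | 72% | 0.40 / 0.02 |

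The 20-per-side rule gives 0.51 inside and 0.08 outside for N = 306 and d = 0.36.

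**Step 4: can a reader tell a false contrast from a real one?** With n = 245, d = 0.36 and a true interaction of 0.36 per SD, the gated refits average 0.57 and 0.01. With no interaction they average 0.54 and 0.07. The refits barely separate the two cases.

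**Step 5: the interaction test alone.** Judged on the full-sample interaction, false moderation is found in 4.7-5.4% of trials per test. With 6 moderators and 2 outcomes, if independent and unadjusted, 1 − 0.95¹² = 46%. For the 5 baseline constructs alone, 1 − 0.95¹⁰ = 40%.

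**The case against.** The strongest reply is that the article describes JN as probing an interaction and as locating where moderation occurred, and that its power statement concerns a significant moderation effect. This reads most naturally as JN after a significant interaction. A condensed article need not spell out that gate, so its absence is not a fault. On that reading a false split is about a 5% event per test. This stands, and the 57-66% should not be quoted as the rate to expect. The gate does not repair the refit, though: the contrast in the refitted effects becomes larger once the interaction has been selected for significance.

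It is also fair that the aim is exploratory, that the simulations replace a latent growth model with one linear regression, and that the ungated rate depends on the split rule and on a non-zero overall effect. These points limit the size of the problem. They do not make the refit valid, because the selection on significance is part of the written procedure.

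A reader might infer three stronger points that the article does not support.

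- *That the subgroup result would decide who is offered the program.* No passage says so. The *Discussion* ties later use to overall efficacy and further evaluation.
- *That JN is wrongly applied to gender.* A two-category moderator has no JN boundary, but the article does not expressly apply JN to it.
- *That there are 18 tests and a 60% chance of a false interaction.* This requires counting drug use frequency and quantity as separate outcomes. With two outcomes the count is 12. Independence is doubtful for related family and stress scales in either case.

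**Conclusion.** The concern holds for the refitting step. It is stated affirmatively in the article, so it is not a detail left to an unseen analysis plan. Whichever way the gate is read, groups are defined by the significance of an effect that is then re-estimated in the same data.

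The size depends on the reading. With a gate, false splits are rare per test (about 5%) but strongly distorted: about 0.51-0.55 inside and 0.07-0.08 outside against a true 0.36. Without a gate, the false pattern appears in about 57-66% of trials at d = 0.36, 26-31% at d = 0.20, and 5-6% at d = 0.

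These figures assume a linear model on a slope score, one normally distributed moderator, a pointwise 5% JN region, and either 245 or 306 analysed youths. The direction of the bias does not depend on those choices; the exact rates do.

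The damage is confined to the exploratory moderation conclusions. It would be wrong to infer that the main efficacy test is compromised, because that test uses the full-sample condition effect on the slope and does not involve the split.

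**What to change.** Delete the step that fits two separate trajectory models. Base any moderation claim on the interaction coefficient and its confidence interval from the full-sample growth model. Show the model-based condition effect with its confidence band across the range of each continuous moderator, and present JN as a description of that plot. For gender, report the interaction and the two model-based effects.

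It would help to state whether JN is produced only after a significant interaction, although once the refit is gone little depends on it. As an option, extend the false discovery rate already named for the outcomes to the moderator tests. This is a reasonable choice for an exploratory family of tests and does not correct an error.

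The cost is a change of wording. It needs no new data, involves less analysis than planned, and leaves the moderation hypothesis testable at about 5% false positives per test before any adjustment.

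### The stated 80% power for moderation (coefficient 0.14, R² = 0.02) does not follow from its printed inputs and conflicts with the main-effect power statement

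*Protocol article*

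**What the plan says.** Both power statements are in the protocol article, Data analysis plan, under the heading Main effects.

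- **Moderation paragraph.** The model works by "regressing the trajectory slope on condition, gender, and the potential baseline moderators, and their interaction". The sample is described as "With a baseline sample size of 306 (assuming 20% attrition rate at each assessment time point". The claim is "we have 80% power to uncover a significant moderation effect (p < .05) when the regression coefficient of the interaction is approximately |0.14", and the size is glossed as "effect size were |0.02| for interaction effect), which is considered a small effect". The figure is attributed to Monte Carlo simulation with 10000 replications.
- **Main-effect power paragraph.** Here the claim is 80% power "to detect a regression coefficient equal to 0.12 (d = 0.36) in the regression of the slope growth factor", "assuming equal sample sizes across both conditions (i.e., 153 cases in each condition) and 20% attrition rate", from the same kind of simulation with condition as the only covariate.

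The article does not say whether the tests are one- or two-sided, whether 0.14 is standardised, how the moderators are scaled, or how much slope variance the other moderation-model terms explain.

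**The concern.** The main effect and the interaction are both single-coefficient tests on the latent slope, in the same 306 families. At equal power, the moderation statement claims to detect an R² of 0.02, about two thirds of the 0.031 implied by the main-effect statement. Its attrition wording is no more favourable. Without a further assumption, both cannot be right.

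The figure matters because the Introduction hypothesises that higher-risk youth will benefit most, and this sentence is what tells a reader how far the trial can test that. If power for a small interaction is nearer 60% than 80%, a non-significant interaction carries less information than the article implies.

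**Working it through.** **Inputs**
- 306 families, 153 per arm; 20% attrition leaves 0.8 × 306 = 244.8, about 245.
- Main effect: coefficient 0.12, d = 0.36, power 80%, Type I error .05.
- Moderation: coefficient 0.14, R² = 0.02, power 80%, p < .05.
- My assumption: two-sided tests, since sidedness is not stated.

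**Step 1: reproduce the main-effect figure.** Families per arm = 2(1.960 + 0.842)² / 0.36² = 121.1, so 122. Dividing by 0.8 gives 152.5, so 153 per arm, which is the planned size. Power with 20% loss is 0.80. A simple formula with error-free slopes therefore reproduces the authors' own figure and is a fair yardstick for the next one.

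**Step 2: put the main effect on the R² scale.** With 1:1 allocation, R² = d²/(d² + 4) = 0.1296/4.1296 = 0.0314. The smallest R² that a one-degree-of-freedom test detects with 80% power at N = 245 is 0.0313. The two agree.

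**Step 3: apply the same test to the interaction.** 0.14² = 0.0196, so coefficient and R² agree if 0.14 is standardised. With f² = R²/(1 − R²) = 0.02/0.98 = 0.0204, noncentrality N × f², and N − 4 denominator degrees of freedom:

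| Families | Power at R² = 0.02 | R² detectable with 80% power |
|---|---|---|
| 306 (no loss) | 0.70 | 0.025 |
| 245 | 0.61 | 0.031 |
| 387 | 0.80 | 0.02 |

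At N = 245 the detectable standardised coefficient is √0.0313 = 0.18. Reaching 387 complete families with 20% loss would need about 387/0.8 = 484 enrolled.

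**Step 4: look for a reading that rescues 80%.**
- *Rounding.* R² = 0.0249 gives 0.70 at N = 245 and 0.796 at N = 306. A standardised coefficient that rounds to 0.14 caps R² at 0.145² = 0.021.
- *One-sided test.* Power is 0.72 at N = 245. It reaches 0.80 only at N = 306 with no attrition, which the article does not assume.
- *Other predictors explain slope variance.* With f² = 0.02/(1 − R² of the full model), 80% needs a full-model R² of 0.38 at N = 245 or 0.225 at N = 306. Taking off the interaction's own 0.02 leaves about 36% and 21% for the other terms.
- *Raw slope units.* The main-effect pair implies a slope SD of 0.12/0.36 = 0.33. With 0/1 condition coding and a moderator of SD 1, a raw 0.14 gives R² = 0.14² × 0.25/0.111 = 0.044 and power 0.92 at N = 245. With a balanced binary moderator such as gender, R² = 0.14² × 0.0625/0.111 = 0.011 and power 0.38. Neither R² is 0.02.

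**The case against.** The strongest reply is that the moderation model is richer than the main-effect model. It contains baseline moderators that may explain slope variance, so equal R² need not mean equal power, and simulation inputs are something an article may leave to a fuller document. This stands in part: a reader might infer that 80% power is unattainable, and the article does not support that. It would hold if the other terms explained about 36% of slope variance at N = 245. That is a demanding assumption but not an impossible one, and it is not printed.

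The second reply is about scale. The main-effect 0.12 cannot be a standardised coefficient, since d = 0.36 corresponds to about 0.18. If 0.14 is also in raw units, the mistake may lie in the R² label and not in the power for that coefficient. This also stands, but the printed pair would then still be wrong.

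A reader might also compound the attrition, 306 × 0.8³ = 157 families, and conclude that the trial would usually miss such an interaction. The article does not support this either. The analysis uses full information maximum likelihood, so partial trajectories contribute, and the wording can equally mean 20% missing at each visit. For linear slopes over the stated visits, assuming slope reliability between 0.3 and 0.9, the information about the slope is worth about 260 to 287 complete families if 20% are missing at each visit, and about 182 to 203 under compounding dropout. The first range lies between the two sample sizes (245 and 306) used in the check; the second would put power below 61%. Neither is 157.

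Finally, moderation is exploratory, and nowhere does the article say that a null interaction will be read as no moderation. That limits the weight of the point, not its correctness.

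**Conclusion.** The point holds as an error in one stated power figure. On the printed inputs, power for R² = 0.02 is about 61% with 245 families and at most about 70% with no attrition, against the 80% claimed. The statement also disagrees with the main-effect statement, whose R² of 0.031 is what the same calculation gives at N = 245.

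This rests on a two-sided 5% test, a standardised 0.14, no other explained slope variance, and slopes measured without error. Unreliable slopes would lower the power figures further. If the simulation used a different scale or substantial explained variance, the 80% may be right for what was simulated, but the article's description would then be incomplete or its R² wrong. The primary analysis and sample size are not affected.

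**What to change.** Reconcile the two power statements by restating the moderation figure, according to what the simulation assumed:

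- **Standardised coefficient, no other explained variance.** Give the detectable interaction as R² of about 0.03 (standardised coefficient about 0.18) at about 245 effective families. Alternatively keep R² = 0.02 and state power of about 60%, at most about 70% without attrition. Note in either case that slope unreliability makes these figures optimistic.
- **Substantial slope variance explained by other terms.** State the amount assumed and its basis.
- **Raw slope units.** Say so, give the moderator's scaling, and correct the R² to match; a continuous and a binary moderator need separate figures.

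Whichever applies, say whether the 20% is missing at each visit or accumulates.

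The cost is one corrected sentence and, on the first reading, a less favourable figure. Design, sample size and analysis model stay as they are.

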## Discussion

In this manuscript, we described the rationale, methods, and design of a randomized controlled trial testing the efficacy of Familias con Orgullo, a family-based intervention designed specifically for HSMY and their families for the prevention/reduction of drug use and depressive symptoms among HSMY. Such interventions that are tailored to the unique needs of HSMY are necessary given the saliency of family and Hispanic cultural values and beliefs for HSMY. The efficacy study described begins to fill a critical gap in the intervention literature because few existing interventions for sexual minority populations have been rigorously evaluated in randomized controlled trials; Familias con Orgullo will be the first family intervention evaluated with HSMY and their families. Familias con Orgullo utilizes parents as the agents of change in preventing and decreasing drug use and depressive symptoms among HSMY. This is notable because current interventions are mainly individual level, and while a few include parents as the agent of change for their youth in the intervention process, none do so with HSMY. Moreover, the interplay of cultural values, minority stressors, family dynamics, and inter- and intra- personal level variables that impact HSMY health will be accounted for and targeted in Familias con Orgullo. Importantly, this intervention was user-centered, such that it was developed based on feedback from HSMY and their parents, ensuring that it is applicable and relevant to their needs.

This study, if successful, will provide evidence that Familias con Orgullo can effectively prevent/reduce drug use and depressive symptoms among Hispanic sexual minority youth. The importance of evaluating interventions such as Familia con Orgullo is highlighted by the National Academies of Sciences, Engineering, and Medicine’s call for research that examines family relationships to further enhance understanding of the well-being of sexual minority populations [49]. Establishing the efficacy of Familias con Orgullo will also pave the way for Familias con Orgullo to be further evaluated, and ultimately implemented and disseminated into community practice, so that it is the standard of care for Hispanic sexual minority youth and begins to ameliorate health disparities related to drug use and depression that impact this vulnerable population.
